#### Data collection

We will use qualitative methods to identify barriers and enablers to physician hand hygiene compliance or non-compliance that can be addressed in a knowledge translation intervention to change (improve) this behaviour. We will conduct semi-structured interviews with key informants – *i.e*., physicians and residents. A semi-structured interview guide, informed by the Theoretical Domains Framework (TDF) [44,45], has been developed and pilot-tested for this purpose (See Additional File 1). The TDF is a behavior change framework that was developed using a systematic consensus approach to simplify psychological theories relevant to behavior change. The framework includes 14 ‘theoretical domains’ derived from 128 constructs from 33 health and social psychology theories that may explain health-related behavior change. The 14 domains offer wide coverage of the potential multi-level determinants of health-related behavior and guide the use of broad prompts that enable interviewees to consider a wide range of possibilities without asking leading questions. Identification of the 14 domains and definitions of each domain is summarized in Table 2. The TDF can be used to inform the choice of potential behavior change techniques to develop interventions as well as to investigate determinants of behavior [44-46]. The TDF-informed interview guide will be used in this project to probe the key informants about reasons they do or don’t adhere to best hand hygiene practices consistently in their clinical practice. This will allow us to identify key beliefs from different domains that could be targeted by knowledge translation interventions to improve their compliance.

**Table 2 T2:** Domains in the theoretical domains framework

**Theoretical Domain**	**Definition [**[44]**]**
Knowledge	An awareness of the existence of something
Skills	An ability or proficiency acquired through practice
Social/Professional Role and Identity	A coherent set of behaviours and displayed personal qualities of an individual in a social or work setting
Beliefs about capabilities	Acceptance of the truth, reality or validity about an ability, talent or facility that a person can put to constructive use
Optimism	The confidence that things will happen for the best or that desired goals will be attained
Beliefs about consequences	Acceptance of the truth, reality or validity about outcomes of a behaviour in a given situation
Reinforcement	Increasing the probability of a response by arranging a dependent relationship, or contingency, between the response and a given stimulus
Intentions	A conscious decision to perform a behaviour or a resolve to act in a certain way
Goals	Mental representations of outcomes or end states that an individual wants to achieve
Memory, attention and decision processes	The ability to retain information, focus selectively on aspects of the environment and choose between two or more alternatives
Environmental context and resources	Any circumstance of a person’s situation or environment that discourages or encourages the development of skills and abilities, independence, social competence, and adaptive behaviour
Social influences	Those interpersonal processes that can cause individuals to change their thoughts, feelings or behaviours
Emotion	A complex reaction pattern, involving experiential, behavioural and physiological elements, by which the individual attempts to deal with a personally significant matter or event
Behavioural regulation	Anything aimed at managing or changing objectively observed or measured actions

We chose to use semi-structured key informant interviews using a theory-based interview guide for three reasons. First, this approach allows participants to respond freely, to illustrate concepts and to present individual perspectives that the interviewer can probe further [47]. Second, a semi-structured interview guide will increase the likelihood that busy participants cover the topics of interest in an efficient manner. Third, such a guide facilitates flexibility, such that an interviewer may explore in greater depth the issues that may arise in the interview that are not addressed by the interview guide [48,49]*.*

The study research assistant (SL), who has been trained in interviewing skills using mock interviews to ensure she is comfortable with the interview guide, will conduct the interviews. Interviews will be audio-recorded (with the participant’s consent) and are expected to last approximately 15–20 minutes. Before beginning each interview, informed consent will be obtained from each key informant. Interviews will be conducted by telephone or in-person, according to the key informant’s preference. Key informants will be given a $20 coffee-shop gift card in appreciation of their time.

#### Data analysis

The interviews will yield a large quantity of data. To monitor the progress of the interviews and permit follow-up of issues that may emerge from the data, interviewing, transcription and analysis will occur concurrently in this phase of the study. The recordings will be transcribed verbatim and verified by the interviewer prior to analysis. Data will be analyzed using NVivo 9, a standard qualitative software program [50]. Interview transcript analysis will involve the following three steps [51,52]:

#### Coding interview transcripts

To facilitate analysis and ensure consistency in coding, two coders will independently code responses from the first two interviews into the TDF theoretical domains (Table 2) and then compare their results to develop a coding scheme. Thereafter, all coding will be guided by the coding scheme. The use of a coding scheme in qualitative analysis is important to reducing subjective bias [53]. The same two coders will code all remaining interviews. The coders will meet frequently (after every five interviews) to review their coding and seek consensus. Coder reliability between the two coders will be assessed using a method proposed by Miles and Huberman [54]: Coder reliability = number of agreements/(total number of agreements + disagreements). In instances of disagreement, we will discuss the rationale behind the coding to come to consensus on an agreed code. Level of agreement between the two coders should meet or exceed 70%, the level of agreement that is considered acceptable to ensure confidence in the coding process [54]. If agreement is not achieved, the text will be allocated into all domains identified by both coders.

#### Generating specific beliefs

Statements describing specific underlying beliefs will be generated for each response within each theoretical domain (of the TDF), by one team member (SL), which will be double-checked by the second coder and also a researcher (JS, JG). We will generate specific beliefs by professional group and specialty: physicians-medicine; physicians-surgery; residents-medicine; and residents-surgery. A specific belief refers to a collection of responses with a similar underlying theme that suggests a problem and/or influence of the belief on the target behaviour [51,52,55]. A frequency count (*i.e*., number of key informants)/belief statement will be derived across the interviews in the four subgroups identified above.

#### Identifying relevant theoretical domains

In line with guidelines previously published [51,52,55], we will judge which of the 14 TDF theoretical domains are relevant to our target behavior. Domains that contain specific beliefs (identified in step two above) that might act as potential barriers or enablers to changing physician hand hygiene behaviour and fulfill the following three criteria will be judged as relevant: relatively high frequency of specific beliefs; presence of conflicting beliefs; and evidence of strong beliefs that may impact on the behavior (our hand hygiene specialist [KS] on the team will help interpret the importance of specific beliefs from a clinical perspective). All three criteria will be considered simultaneously in determining relevance of the theoretical domains.

Findings from this analysis will be used in two ways. First, we will use the data to develop a rich description of physicians’ views on the factors influencing their hand hygiene compliance. Second, we will use the findings to develop a theory-based knowledge translation intervention to improve the behaviour (see Phase 2).

#### Non-participant observation

Concurrent with the key informant interviews, we will conduct non-participant observation to identify any additional perceived (by the observer) barriers and enablers to physician hand hygiene compliance not identified in the semi-structured interviews conducted with physician and residents. We will collect this data by observing physicians during routine hospital hand hygiene audit sessions, which includes interaction between the auditor and physicians/residents. We will observe both the environmental context of the interactions as well as the process of the interactions. The assessment will be guided by an observation checklist (Table 3). Two team members (SL, JS) will conduct the non-participant observation by accompanying a hospital-trained auditor on a minimum of four routine sessions; a minimum of two sessions at each of the two hospital campuses sampled in the study will be attended. Field notes will be compiled, transcribed and then analyzed using qualitative content analysis. Qualitative content analysis focuses on unique themes found within the text, rather than the statistical significance of key words or concepts as in quantitative content analysis [56]. We will follow the same principle of ‘data saturation’ used with the interviews, observing audit sessions until no new barriers or enablers to physician compliance with hand hygiene are identified [43,57]. Prior to conducting the non-participant observation, the two data collectors will attend an auditor training session to gain further insight into the process.

**Table 3 T3:** Non-participant observation checklist

**Observation of the environmental context of interactions**	**Observation of the process of the interaction**
Who is present during the interaction?	Who speaks to whom and about what? (*i.e*., the auditor and physician interaction)
Physical space (use a diagram to depict the set up of space and how people, patients and sinks/alcohol hand rub dispensers are positioned in that space)	How are concerns responded to?
Describe how patient care is delivered in the setting (*i.e*., is this a shared room? Are other patients receiving care at the same time?)	Are the physicians receiving feedback from the auditors?
Location of the auditor in relation to the physician being observed	If feedback is given, how do the physicians respond?
Describe the length of the interaction	Whenever possible, capture verbatim accounts between individuals present

#### Focus groups with hand hygiene experts

We will also conduct focused discussions with hand hygiene experts (*e.g*., hand hygiene auditors, infection control specialists, and members of senior management) using a modified version of the TDF-based interview guide used with the key informants. The Associate Director of Infection Prevention and Control (KS) will request volunteers for the focus groups from each campus. We will target 6–8 participants per focus group and a total of two focus groups (60–90 minutes each; one focus group per campus). Two members of the research team (SL, JS) will conduct the focus groups with one team member acting as a moderator and the other as an observer/recorder. Each focus group will be audio-recorded and transcribed. The transcripts will be checked for accuracy before analysis. Analysis will follow the same procedure outlined previously for key informant interviews (double coding of interview transcripts, generation of specific beliefs, and identification of relevant theoretical domains).

#### Phase 2: Design of a theory-based knowledge translation intervention to improve physician hand hygiene compliance

Using the data obtained in Phase 1 (identification of barriers and enablers to physician hand hygiene compliance), we will develop a theory-based knowledge translation intervention that encompasses behavior change techniques to overcome the identified barriers and enhance the enablers to hand hygiene compliance by physicians. The intervention will be developed using intervention mapping, a formal systematic process for building interventions based upon identified barriers and enablers to behaviour change [58]*.* In this process, the TDF theoretical domains identified as relevant in Phase 1 (in the interviews with physicians and focus groups with hand hygiene experts) will be prioritized. We will also consider any additional barriers identified in the non-participant observation sessions. A range of behaviour change techniques will be selected to address the most important domains (barriers to hand hygiene compliance). We will use the Behavior Change Matrix [59], developed by Michie and colleagues, in this process. The Behavior Change Matrix consists of a list of 53 effective behaviour change techniques, determined based on expert consensus and systematic review, mapped onto the TDF domains. This approach simplifies the diverse science of behaviour change into a taxonomy of behaviour change techniques that can be used to design knowledge translation interventions with well-articulated causal pathways [59].

The behavior mapping process explicates the program logic of the resulting intervention by explicitly linking behaviour change techniques to the barriers that participants target. The intervention techniques we choose and their delivery in the pilot (Phase 3) will be based upon: empirical evidence and expert consensus of the effectiveness of the behavior change techniques; what is likely to be feasible in our specific context; and what is locally relevant and acceptable. The investigative team, which includes researchers and clinicians, will be involved in the design of the intervention. We will hold a series of team meetings to carry out the mapping process and to design and plan the implementation of the intervention.

#### Phase 3: Implementation and pilot of the intervention

We will pilot the theory-based knowledge translation intervention determined in Phase 2 of our work in four patient care units at the same large urban hospital used to collect our data on barriers and enablers. Routine hand hygiene audits collected by the hospital will be used to determine which units are ‘low performing.’ We will randomly select for the pilot, from all ‘low performing’ medical and surgical units, two medical and two surgical units (divided equally between campuses). We will assess effectiveness of the intervention using pre- and post-hand hygiene audits (counts of physicians/residents who washed their hands in accordance with current guidelines), which will be collected by hospital-trained auditors. We will report pre- and post-audit numbers and perform a chi-square test to examine differences between proportions of physicians/residents performing appropriate hand hygiene pre- and post- intervention if there is sufficient sample size (*i.e*., sufficient numbers of physicians/residents audited on each unit). An important element of our evaluation in Phase 3 will be a process evaluation to understand what aspects of the intervention did and did not work. The process evaluation will involve interviews with clinicians (*e.g*., physicians, residents, nurses) on the pilot units as well with hand hygiene experts across the hospital. We will conduct interviews with up to five residents and staff physicians per piloted unit. In the focus group, we will target six to eight hand hygiene experts [60]. We will follow the same process for conducting the focus groups as previously outlined. All process interviews and focus groups will be analyzed using thematic content analysis.

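### Pilot units are picked for low routine audits and then judged by an uncontrolled pre/post audit comparison; if the selecting audits are reused as baseline, regression to the mean can look like an intervention effect

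*Protocol article*

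**What the plan says.** Everything that fixes the design is in the protocol article under Phase 3: Implementation and pilot of the intervention.

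- **Eligibility:** "Routine hand hygiene audits collected by the hospital will be used to determine which units are ‘low performing". No cut-off, audit period or number of observations is attached to the label.
- **Draw:** "We will randomly select for the pilot, from all ‘low performing’ medical and surgical units, two medical and two surgical units", split equally between the campuses.
- **Setting:** the pilot runs "in four patient care units at the same large urban hospital used to collect our data on barriers and enablers". No unexposed units are described.
- **Outcome:** effectiveness is assessed with "pre- and post-hand hygiene audits (counts of physicians/residents who washed their hands in accordance with current guidelines), which will be collected by hospital-trained auditors".
- **Analysis:** the audit numbers are reported for both periods. The plan is also to "perform a chi-square test to examine differences between proportions of physicians/residents performing appropriate hand hygiene pre- and post- intervention", provided there are "sufficient numbers of physicians/residents audited on each unit".

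The section on non-participant observation describes researchers accompanying a hospital-trained auditor on routine sessions, so the same kind of staff conduct the routine audits and the pre/post audits. The limitation paragraph of the Discussion covers the effect of being observed and the training of auditors. It does not mention selection on a low starting value.

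**The concern.** The selection variable and the outcome are the same kind of measurement. A unit's observed compliance is its true rate plus sampling error, and choosing units with low observed values also picks out those whose error happened to be negative. The next audit carries fresh error, so on average it moves back up.

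Drawing at random within the low group does not help, because every unit in that group got there through a low observed value. Without comparison units the rise cannot be told apart from an effect, and a chi-square test on the pooled counts treats it as signal.

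At stake is what the pilot reports about the intervention. The article says "We will assess effectiveness of the intervention using pre- and post-hand hygiene audits", and it plans to refine the piloted intervention for a multi-site cluster randomised trial. An inflated gain would carry into that planning.

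**Working it through.** The article gives no sample size, significance level or effect size for Phase 3, so there is no planned figure to reproduce. The check is how large an artefact the design permits when the true effect is zero.

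**Input from the article (Background).** Local physician compliance was 65–69% in March 2011 (midpoint 67%), and the corporate goal is 80%. The gap is 80 − 67 = 13 points.

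**Assumptions, not in the article.** 20 candidate units; true between-unit SD 8 points; 20 to 100 audits per unit per period; selecting audits reused as the pre measurement; two-sided 5% test. Two meanings of low are tried: the lowest third of units, and below the 80% goal.

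**Closed form (normal approximation).** Let e = 0.67 × 0.33 / n be the sampling variance and T = √(0.08² + e) the SD of observed unit rates. Let h be the mean distance of the selected units below the overall mean, in units of T. Then

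expected spurious gain = h × e / T.

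For the lowest third, h = 1.09. For a cut at 80%, h = φ(c)/Φ(c) with c = 0.13/T.

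- n = 20: e = 0.01106, T = 0.132. Lowest third: 1.09 × 0.01106 / 0.132 = 9.1 points. Below 80%: c = 0.98, h = 0.29, giving 2.5 points.
- n = 100: e = 0.00221, T = 0.0928. Lowest third: 1.09 × 0.00221 / 0.0928 = 2.6 points. Below 80%: c = 1.40, h = 0.16, giving 0.4 points.

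**Simulation of the same model** (Normal unit rates, binomial audits, lowest third taken as six of 20, four units drawn at random, pooled test, no true effect). False improvement is a significant result in the direction of improvement, nominally 2.5%.

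| Audits per unit | Lowest third: gain (points) | False improvement | Below 80%: gain (points) | False improvement |
|---|---|---|---|---|
| 20 | 9.5 | 19% | 3.0 | 4.3% |
| 30 | 7.1 | 18% | 1.8 | 3.8% |
| 50 | 4.9 | 15% | 0.9 | 3.7% |
| 100 | 2.7 | 11% | 0.35 | 3.1% |

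At 20 audits the below-80% gain exceeds the closed form because the counts are discrete: below 80% then means at most 15 of 20, which is 75%.

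**A different selection model.** One unit is drawn from the low units in each of four campus-by-specialty strata of four units. The SD is 5 or 10 points, and low means the bottom half, the bottom quarter, below 65% or below 60%. The spurious gain is 4.9–9.8 points at 20 audits per unit, 2.4–5.5 at 50, 1.2–3.3 at 100 and 0.7–1.9 at 200. False improvement ranges from 4.1% to 21%.

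**With a separate baseline.** In that second model, a fresh pre audit brings the mean change to within 0.1 point of zero and the two-sided rejection rate to 4.3–5.0%. In the 20-unit model it gives about 0 points and 2.5% false improvement. Both results assume that a unit's true compliance is stable between audits.

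**The case against.** A reader might infer that the selecting audits are the pre data, and hence that regression to the mean will appear as an effect. The article does not say that. It mentions the routine audits first, as the basis for labelling units, and then pre and post audits "which will be collected by hospital-trained auditors". Order and tense fit a new baseline taken after the draw as well as they fit reuse. Shared auditors suggest a shared audit programme, not shared observations. On the separate-baseline reading the quantified artefact disappears. This stands, and it is why the point is conditional.

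The size is also open. The only benchmark in the article is the 80% goal. If that defines low, most units qualify, selection is weak and the artefact is small. The largest figures need about 20 audits per unit, where the condition on sufficient numbers may stop the test from being run. Both remarks stand, although the pre and post audit numbers are reported whether or not the test is done.

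It can further be said that audit dates are detail which an article leaves to a fuller document. That is true of the dates. But selection on low audits and an uncontrolled pre/post comparison of the same measure are design choices fixed in this text, and a later analysis plan cannot supply a baseline window that was never collected.

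Finally, this is an exploratory pilot with a process evaluation, and no go/no-go rule hangs on the test. That lowers the consequence. It does not remove it, since the stated purpose of the audits is to assess effectiveness.

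**Conclusion.** The point holds in conditional form. The article selects units on low routine audits, compares the same kind of audit before and after without a control, and leaves open whether the selecting audits double as baseline. If they do, the expected bias is towards improvement.

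Under the 20-unit assumptions, the bias is about 9 to 3 points at 20 to 100 audits per unit when low means the lowest third, and about 3 to 0.3 points when it means below 80%. The 13-point gap to the goal gives the scale. None of these sizes is an estimate for this hospital, because the number of units, their true spread, the audits per unit and the meaning of low are all assumed. The documents do not support the claim that the bias will occur or that it will be large.

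A fresh baseline removes the sampling-error part only. Real short-term fluctuation in a unit's compliance, and any continuing rise like the one from 14–17% to 65–69% described in the Background, would remain in a pre/post difference.

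**What to change.** 1. State that audits used to classify units as low performing are excluded from the pre measurement.
2. Take the baseline from an audit window that opens after the four units are drawn and closes before the intervention starts.
3. Report the routine audits of the undrawn low-performing units over the same pre and post windows, descriptively, as a reference for real fluctuation and background trend. How informative this is depends on how many such units remain after the draw.

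The cost is a possible short delay before the intervention starts, within a study planned for one year, and a little more tabulation of audits the hospital already collects.

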## Background

Healthcare-associated infections are ranked by the World Health Organization as one of the top 10 causes of hospital deaths worldwide [1]. In Canada, they are the most common serious complication of hospitalization, affecting 10% of all patients in acute-care hospitals [2] and are the fourth leading cause of death [3]. Healthcare-associated pathogens that can lead to infection are transmitted through direct and indirect contact, droplets, air, and the contaminated hands of healthcare workers (HCWs), the latter being the most common vehicles of transmission in most settings [4]. Microorganisms are known to survive on hands for up to 60 minutes following contact with a patient or contaminated surface. Hand contamination increases with increasing time spend providing direct patient care, in the absence of appropriate hand hygiene [4].

Hand hygiene, defined as the act of washing one’s hands with soap and water or disinfecting them with an antiseptic agent, is the single most successful and cost-effective means of preventing healthcare-associated infections, as well as an effective means of preventing illness in the community that may lead to hospitalization [5-8]. Hand hygiene, before and after all patient or patient environment contact, before aseptic procedure, and/or after bodily fluid exposure, is recommended in all published infection control and public health guidelines and is considered the standard of care for all HCWs [5-10]. Yet many studies document that HCWs’ compliance with hand hygiene recommendations is consistently less than 50% [6,11-15], with compliance among physicians routinely lower than that of other HCWs [16-19]. Locally, at the Ottawa Hospital (proposed for this study), physician hand hygiene compliance rates have increased significantly from 14–17% between 2004–6 to 65–69% in March 2011. In spite of this increase, however, physician compliance continues to lag behind that of most other occupational groups and is below the corporate goal of 80%.

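### Phase 3 judges effectiveness from an uncontrolled pre/post audit comparison, so any continuing background rise, or regression to the mean, would be counted as intervention effect

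*Protocol article*

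**What the plan says.** All references are to the protocol article.

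- **Comparison.** The Phase 3 section states: "We will assess effectiveness of the intervention using pre- and post-hand hygiene audits". It will report the pre and post numbers and "perform a chi-square test to examine differences between proportions of physicians/residents performing appropriate hand hygiene pre- and post- intervention", the test being conditional: "if there is sufficient sample size". It names no comparison units and no allowance for trend.
- **Selection of units.** "Routine hand hygiene audits collected by the hospital will be used to determine which units are ‘low performing". Then: "We will randomly select for the pilot, from all ‘low performing’ medical and surgical units, two medical and two surgical units", divided equally between campuses.
- **Background trend.** The Background section says of the study hospital that "physician hand hygiene compliance rates have increased significantly from 14–17% between 2004–6 to 65–69% in March 2011". It adds that physicians remain below a corporate goal of 80%.
- **Limitations.** The Discussion names measurement of the behaviour as a limitation, including the effect of being observed. It does not mention background trend or the lack of a comparison.
- **Status of Phase 3.** Methods and Discussion place it at phase 2 of the MRC framework (exploratory studies), before a planned multi-site cluster randomised trial.

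**The concern.** Post minus pre in the pilot units adds together the intervention effect, any change that would have happened anyway and, possibly, a selection artefact.

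The article supplies a reason to expect the second: a large earlier rise at this hospital and an unmet institutional target. It also creates the conditions for the third. Units picked because their audited compliance was low will on average look better at the next audit, even if nothing changes. That affects the result if the audits used to pick the units are also the pre measurement, which the article leaves open.

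Both terms favour the intervention. At stake is the reading of the pilot: a favourable change, with or without a small p-value, could not be attributed to the intervention, yet the text calls the exercise an assessment of effectiveness.

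**Working it through.** The article gives no sample size, power or significance level for Phase 3, so there is no figure to reproduce. The check asks how often the planned test would reject if the intervention did nothing and only background drift acted.

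**1. Average past rise (Background figures).** Dates as decimals: March 2011 = 2011.2, middle of 2004–6 = 2005.5, its start = 2004.0, its end = 2007.0.
- Midpoints: (67 − 15.5) / 5.7 = 9.0 points per year
- Lowest: (65 − 17) / 7.2 = 6.7
- Highest: (69 − 14) / 4.2 = 13.1

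**2. Drift between audits.** The gap is not stated. All three phases are to fit in one year, so 3 and 6 months are assumed.
- 3 months: 9.0 × 0.25 = 2.25 points (range 1.7 to 3.3)
- 6 months: 9.0 × 0.5 = 4.5 points (range 3.3 to 6.5)

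**3. Rejection rate with no intervention effect.** Assumed: true pre compliance 55%, two-sided 5% level, independent observations, n per period. With p̄ the mean of the two proportions p₀ and p₁, and d = p₁ − p₀:

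se₀ = √[2p̄(1 − p̄)/n], se₁ = √[(p₀(1 − p₀) + p₁(1 − p₁))/n]

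P(reject) = Φ[(d − 1.96 se₀)/se₁] + Φ[(−d − 1.96 se₀)/se₁]

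Example, 6 months, n = 200: p₀ = 0.55, p₁ = 0.595, se₀ = 0.0495, se₁ = 0.0494. The terms are Φ(−1.05) = 0.147 and Φ(−2.87) = 0.002, total 14.9%.

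| n per period | 3 months (55% to 57.25%) | 6 months (55% to 59.5%) |
|---|---|---|
| 100 | 6.2% | 9.8% |
| 200 | 7.4% | 14.9% |
| 400 | 9.8% | 25.1% |
| 800 | 14.8% | 44.4% |

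With no drift the rate is the nominal 5%.

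**4. Regression to the mean.** Simulation with assumed inputs: 20 units, mean compliance 67%, the lowest 7 called low performing, between-unit SD 5 or 10 points, 25 to 100 audits per unit. If the selection audits are reused as the pre measurement, the apparent gain is 2.1 to 8.5 points with no true change. If fresh pre audits are taken, this term disappears.

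**5. Effect of a concurrent comparison.** Simulation with four pilot and four undrawn units (the second number is assumed), 60% baseline, 25 to 100 observations per unit per period, drift of 0 to 8 points. A t-test on unit-level changes rejected in 4.3–5.3% of runs in every setting. At 5 points of drift with no between-unit variation in change, the pooled pre/post chi-square rejected in about 11%, 18% and 30% of runs for 25, 50 and 100 observations per unit.

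**6. Precision of that contrast.** At 50 observations per unit per period and 60% compliance, the variance of one unit's change is 2 × 0.24/50 = 0.0096. For the difference between two means of four it is 2 × 0.0096/4 = 0.0048, so the SE is 6.9 points and the 95% half-width about 1.96 × 6.9 = 13.6 points, before any between-unit variation.

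**The case against.** **It is an exploratory pilot.** This stands. The chi-square is conditional on numbers, a process evaluation is an important part of Phase 3, and no decision rule hangs on the test. A reader might infer that a spurious success would carry an untested intervention into the cluster trial. The article does not support that: it plans to refine the piloted intervention for that trial whatever the audits show, and the trial is where effectiveness is to be tested.

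**The rise may have stopped.** A reader might infer that compliance is rising steeply at the time of the pilot. The Background gives two time points, the later in March 2011, for the hospital's physicians overall and not for lagging units. Continued rise is plausible, not shown. The planned comparison cannot tell either way.

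**The larger rejection rates rest on assumptions.** Correct. A 6-month gap and 400 to 800 observations are favourable to the concern. At 3 months with 100 to 400 observations the excess over 5% is small.

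**A ready-made randomised control is not established.** A reader might infer one from the random draw. The text says "two medical and two surgical units (divided equally between campuses" but not that one unit is drawn per specialty-by-campus cell, nor how many low-performing units exist. Some cells may have none left over. It does not say whether the pilot audits are the routine ones or extra, so routine data elsewhere may not be comparable. Residents work across campuses and may carry the intervention with them.

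**Observation effects are disclosed.** They are, and both periods are audited, so this point does not rest on them.

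What remains is that the stated comparison cannot separate intervention from background change, and that this is not acknowledged.

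**Conclusion.** The point holds as a cheap improvement, not as a must-fix. As written, Phase 3 would credit to the intervention any continuing rise in compliance, and any regression to the mean if selection audits double as the pre measurement. The direction of the bias depends only on those two conditions.

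Its size cannot be fixed from the article. The figures in the table hold if the past average rise continued unchanged, the true pre level was 55% and observations were independent. The 2 to 8.5 points for regression to the mean rest wholly on assumed unit numbers and spread. None of these figures should be quoted as the trial's actual error rate.

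**What to change.** 1. Extract routine physician audit data, over the same pre and post windows, for the low-performing medical and surgical units not drawn. Use the same kind of audit for both groups; if the pilot-unit audits are extra, use the routine audits for both.
2. Report the difference in change (pilot minus undrawn units) with a confidence interval, as an exploratory estimate, by specialty and campus where units allow. On average this removes the shared trend and the shared selection.
3. Where no undrawn low-performing unit exists, show other units as trend context only. They were not selected for low compliance and do not share any regression to the mean.
4. If no comparable data exist, replace 'assess effectiveness' with 'describe change' and state background trend as a limitation.

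**Cost.** A data extract and a paragraph of analysis text, or a wording change alone. Downsides: residents working across campuses may dilute the contrast towards no effect, audit counts in the undrawn units may be uneven, and precision will be low.
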